### Study aims

The study main aims are: 1) To assess the prevalence of significant liver fibrosis (LSM ≥6.5 kPa) using VCTE, and that of NAFLD (≥225 dB/m) using the CAP in children and adolescents; and 2) To determine the optimal cut-off points of the CAP to achieve maximum concordance with the MRI findings in the diagnosis of mild, moderate and severe liver steatosis in children and adolescents.

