LSM is performed in all patients using VCTE with the Fibroscan® (FS) system (Echosens, France). LSM is performed with S, M or XL probe following the Automatic Probe Selection tool available on the FS. The FS used is the 430 MINI. FS measures the hepatic elasticity of a cylinder approximately 1 cm in diameter by 4 cm in length [41]. FS transmits, via a probe, a vibration that propagates through the liver. The speed of propagation of the vibration correlates with the stiffness (in kPa) of the liver tissue and allows estimation of the fibrosis degree. In order for VCTE to be valid, 10 correct determinations with an interquartile range (IQR) <30 and a success rate >60% must be obtained. Significant liver fibrosis by VCTE is being defined by a LSM ≥6.5 kPa [13–16].Fibrosis scores/serum biomarkers: Pediatric NAFLD Fibrosis Index (PNFI) and Pediatric NAFLD Fibrosis Score (PNFS) are being used to estimate fibrosis degree. Significant liver fibrosis is being defined when the values of the different scores are above the following cut-offs, according to literature: PNFI ≥9, PNFS ≥13 [22, 23, 42, 43].

**Liver steatosis** is estimated using three methods: CAP, liver steatosis score and MRI.

CAP using VCTE is used to measure liver steatosis with the FS using either S, M or XL probe at the time of LSM. Liver steatosis is diagnosed when the value of CAP ≥225 dB/m [13–16].Liver steatosis is measured by the steatosis score Fatty Liver Index (FLI) which is based on: WC, BMI, TG and GGT [19]. Significant liver steatosis is defined when FLI ≥60 according to literature [44].Liver steatosis measured by MRI. It is performed using the Magneton Essenza 1.5 Tesla Aera system (SIEMENS), with the integration of Tim technology and Dot Engines (Day Optimizing through put Engines) application packages. The result obtained is the steatosis score or steatosis degree corresponding to the percentage of hepatocytes containing fatty vacuoles with respect to the hepatic fat fraction. Thus, a differentiation is made among mild steatosis (5–29% of hepatocytes affected), moderate steatosis (30–59% affected) and severe steatosis (more than 60% of hepatocytes affected). MRI is performed on all participants with altered VCTE results (≥6.5 kPa and/or ≥225 CAP) and 10% of participants with normal VCTE results (<6.5 kPa or <225 CAP).

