### Sample size calculation

The school population aged between 9 and 16 in Mataró stands at 11,503 individuals [45]. These are approximately equally distributed between the 4 groups: male/female between 9 to 12 and 13 to 16 years old.

We expect that 8% of this population will have NAFLD and 2% will have liver fibrosis. A sample size of 2,866 students will allow us to estimate a prevalence of NAFLD stratified by age (9–12, 13–16 years) and sex of 8%, with a precision of 2% in each stratum, and a prevalence of fibrosis of 2%, with a precision of 1% in each stratum. We anticipate that blood samples will be available in 50% of the sample and MRI in 70%. MRI will be offered to all LSM/CAP positive subjects (LSM ≥6.5 kPa / CAP ≥225 dB/m) and, randomly, to 10% of those with negative LSM/CAP (LSM <6.5 kPa / CAP <225 dB/m). This will add up to 1,433 blood tests and 424 MRIs.

With the proposed sample we can find a concordance of 80% with a precision of 4% using kappa indices, or an intraclass correlation coefficient of 0,8 with a precision of 2,5% (8% and 4% precision for kappa and ICC, respectively, using only 424 MRIs). This sample size has been calculated assuming a design effect of 20%, an alpha error of 5%, a power of 80% and bilateral contrasts.

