### Statistical analyses

Prevalences of NAFLD and fibrosis will be calculated using CAP ≥225dB/m and LSM ≥6.5kPa, respectively. They will be calculated by sex and age (9–12 and 13–16 years) and 95% confidence intervals will be provided.To determine the optimal CAP cut-off point that best fits the 4 MRI categories, the relationship between CAP and MRI will be explored graphically, CAP means for each MRI category will be compared by ANOVA, 2-to-2 ROC curves will be used, and a multi-class ROC curve will be used to obtain the overall area under the curve for the finally chosen points. In addition, dichotomous CAP classifications (normal/altered) will be compared with MRI levels using contingency tables and chi-square tests.To identify the variables related to NAFLD, multivariate models will be used using NAFLD as the dependent variable and possible risk and confounding factors as independent variables.Concordance between the diagnosis of NAFLD or fibrosis obtained by different methods (CAP vs FLI, LSM vs PNFI, LSM vs PNFS) will be assessed by kappa indices (when using the dichotomised version of these variables) and by the intraclass correlation coefficient (when using the continuous version of the variables). The best cut-off point in PNFI and PNFS will be chosen to detect fibrosis using LSM ≥6.5 kPa as the standard test in the diagnosis of fibrosis using ROC curves.The construction of the biomarker to detect the presence of steatosis in children and adolescents will be carried out using the coefficients of multivariate logistic regression models, where steatosis (CAP >225 dB/m) will be the dependent variable and the rest of the variables will be potential explanatory variables that may form part of the marker.

To take into account that participants come from selected schools, hierarchical models will be used when necessary. All tests will be bilateral, with a significance of 5%. We do not plan to use missing data imputation methods as we expect very few missings beyond those already considered. Stata17 statistical package will be used.

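### The MRI grades behind the CAP cut-offs are set in percentages of hepatocytes, a quantity MRI does not measure, with no limits or conversion on the fat-fraction scale

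*Protocol article*

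**What the plan says.** The second main aim (Study aims) is to find CAP cut-offs that give "maximum concordance with the MRI findings in the diagnosis of mild, moderate and severe liver steatosis in children and adolescents". Main outcome measures lists both the accuracy of CAP against MRI and the cut-offs themselves. Statistical analyses states the task as "To determine the optimal CAP cut-off point that best fits the 4 MRI categories". The four categories are no steatosis plus the three grades. The tools named are ANOVA, pairwise ROC curves and a multi-class ROC curve.

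The grades are defined under Data collection and measuring tools, in the text on liver steatosis. The MRI result is described as a "steatosis degree corresponding to the percentage of hepatocytes containing fatty vacuoles with respect to the hepatic fat fraction". The bands follow: "mild steatosis (5–29% of hepatocytes affected), moderate steatosis (30–59% affected) and severe steatosis (more than 60% of hepatocytes affected"). No source is cited for them, although the same section cites sources for the LSM, CAP, FLI, PNFI and PNFS thresholds.

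Sample size calculation plans 424 MRIs and judges them by the precision of kappa and the ICC. It gives no expected number of children per MRI grade.

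**The concern.** The share of hepatocytes that contain vacuoles is counted under a microscope. A hepatic fat fraction is an amount of fat in the liver. The article's definition, "percentage of hepatocytes containing fatty vacuoles with respect to the hepatic fat fraction", joins the two as if they were one number. Biopsy is not part of the MRI comparison, so nothing in the described design supplies a hepatocyte percentage. What the scanner can supply is a fat fraction, and for that the article gives no limits.

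The grades are the reference standard for a main aim. If their limits are not fixed in the unit that is measured, two imaging centres could grade the same scan differently, and a published CAP cut-off for moderate or severe steatosis would have no definite fat content behind it. This holds whatever the distribution of liver fat in the cohort. A second consequence is conditional: if readers put the 30% and 60% limits straight onto a fat fraction, few children might reach the upper two classes.

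The bands also leave a gap, since moderate ends at 59% and severe begins above 60%. A value of exactly 60% belongs to no grade.

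**Working it through.** **1. How many scans feed the comparison.** Inputs from Sample size calculation: N = 2,866, expected NAFLD 8%, MRI availability 70%, and a 10% random sample of negatives.

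- Scanned positives: 0.70 × 0.08 × 2,866 = 160
- Sampled negatives: 0.10 × 0.92 × 2,866 = 264
- Total: 160 + 264 = 424, the plan's figure

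The plan's number is reached with the 70% applied to the positives only. About 160 CAP-positive children are therefore the main source of moderate and severe cases.

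**2. What those 160 can support.** The article gives no grade distribution. The severe shares below are assumptions. The 95% half-width for a true sensitivity of 0.80 is 1.96 × √(0.80 × 0.20 / n).

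| Assumed severe share of 160 | Severe children | Half-width for sensitivity 0.80 |
|---|---|---|
| 10% | 16 | 1.96 × √(0.16/16) = 0.20 |
| 5% | 8 | 1.96 × √(0.16/8) = 0.28 |
| 2.5% | 4 | 1.96 × √(0.16/4) = 0.39 |

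A severe class of 20 would need 20/160 = 12.5% of the scanned positives to be severe. The highest cut-off is thus imprecise even with a fairly generous share.

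**3. Illustration if the bands are read as fat fractions.** Assume that fat fraction in the 160 is lognormal, truncated below at 5% (the lower limit of mild), with median m (before truncation) of 8 to 15% and log-SD s of 0.5 to 0.7. With S(x) = 1 − Φ(ln(x/m)/s), the expected count at or above x is 160 × S(x)/S(5).

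Central case, m = 10 and s = 0.6:

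- S(5) = 0.876, S(30) = 0.0335, S(60) = 0.00141
- At 30% or more: 160 × 0.0335/0.876 = 6.1
- Above 60%: 160 × 0.00141/0.876 = 0.26

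| m, s | At 30% or more (includes severe) | Above 60% |
|---|---|---|
| 8%, 0.5 | 0.8 | 0.01 |
| 10%, 0.6 | 6.1 | 0.26 |
| 15%, 0.7 | 27.4 | 4.05 |

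**4. Sensitivity to the truncation point.** The Introduction says CAP quantifies hepatic fat above 11%, without naming the scale. If that is a fat fraction and the CAP-positive children are truncated there instead, the ranges become 2.5 to 38.4 at 30% or more and 0.02 to 5.7 above 60%. The central case at 30% or more roughly doubles, to 12.3.

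**5. What does not depend on any of this.** The none-versus-mild contrast turns on the 5% limit alone and can draw on all 424 scans.

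**The case against.** The best defence is that the wording allows for a conversion. The article says the MRI degree corresponds to a hepatocyte percentage, which could mean that MRI output is first mapped to histology-equivalent grades. On that reading nobody applies 30% and 60% to a raw fat fraction. The reading is possible, but no mapping is stated or cited, so it leaves the reference standard unfixed. The unit problem stands either way.

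A reader might go further and infer that the moderate and severe classes will be almost empty, that their cut-offs cannot be derived and that the second aim fails. The documents do not support this. It requires direct use of the bands on fat fraction, which the article does not state, and high fat fractions to be rare in these children, on which it gives no data. The illustrative count at 30% or more varies about 35-fold (0.8 to 27.4) over plausible inputs and rises with a different truncation. At its upper end about 23 children would be moderate (27.4 − 4.05), which is not an empty class. The first cut-off and the overall comparison of CAP with MRI remain deliverable.

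It can also be said that a condensed article leaves imaging detail to the full protocol. That is fair for acquisition and reading procedures. Here, however, the article does state the grading rule, and states it in a unit the comparator does not produce.

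**Conclusion.** The definition is wrong and should be corrected before the CAP analysis. The grades that serve as reference for a main aim are expressed as hepatocyte percentages, equated with a fat fraction, and have no limits in MRI units. This conclusion follows from the text and from the fact that MRI yields a fat fraction rather than a cell count. It needs no distributional assumption.

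The consequence for class size is conditional. If the bands are applied directly to the fat fraction, the moderate and severe classes may be too sparse for their cut-offs: roughly 1 to 27 of about 160 children at 30% or more, and 0 to 4 above 60%, under the assumed lognormal range. The risk is confined to the two upper cut-offs. The unassigned value of 60% is a minor slip in the same sentence.

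**What to change.** In the liver steatosis text of Data collection and measuring tools:

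- Define the MRI result as the hepatic fat fraction in percent, recorded as a continuous value, and remove the percentage of hepatocytes as an MRI result.
- Replace the three bands with contiguous grade limits on the fat-fraction scale, with a cited source, fixed before CAP is analysed, so that every value falls in exactly one grade.

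In Statistical analyses:

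- Keep the grade cut-offs as the main analysis, since the aim is defined that way, and add CAP against continuous fat fraction as a supporting analysis.
- State that moderate and severe will be reported combined if either class is too small to support its own cut-off.

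The cost is mainly wording; no extra children or scans are needed. There are two drawbacks. The grades will no longer share the limits of biopsy grades. The change also assumes that the acquisition yields a fat fraction. The text implies this, but it names no sequence and data collection had already begun, so the sponsor should confirm that the value was stored or can be recovered from the images.

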### Sample size calculation

The school population aged between 9 and 16 in Mataró stands at 11,503 individuals [45]. These are approximately equally distributed between the 4 groups: male/female between 9 to 12 and 13 to 16 years old.

We expect that 8% of this population will have NAFLD and 2% will have liver fibrosis. A sample size of 2,866 students will allow us to estimate a prevalence of NAFLD stratified by age (9–12, 13–16 years) and sex of 8%, with a precision of 2% in each stratum, and a prevalence of fibrosis of 2%, with a precision of 1% in each stratum. We anticipate that blood samples will be available in 50% of the sample and MRI in 70%. MRI will be offered to all LSM/CAP positive subjects (LSM ≥6.5 kPa / CAP ≥225 dB/m) and, randomly, to 10% of those with negative LSM/CAP (LSM <6.5 kPa / CAP <225 dB/m). This will add up to 1,433 blood tests and 424 MRIs.

With the proposed sample we can find a concordance of 80% with a precision of 4% using kappa indices, or an intraclass correlation coefficient of 0,8 with a precision of 2,5% (8% and 4% precision for kappa and ICC, respectively, using only 424 MRIs). This sample size has been calculated assuming a design effect of 20%, an alpha error of 5%, a power of 80% and bilateral contrasts.

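### The 4% precision stated for a kappa of 0.80 does not hold for the three planned kappa comparisons: at 1,433 blood samples it is about 6 points for steatosis and 12 for fibrosis

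*Protocol article*

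**What the plan says.** The sample size section of the protocol article gives one kappa precision for the study: "With the proposed sample we can find a concordance of 80% with a precision of 4% using kappa indices". It adds a second for the imaging subset: "8% and 4% precision for kappa and ICC, respectively, using only 424 MRIs". No prevalence is attached to either figure, and steatosis and fibrosis are not separated.

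The same section supplies the other inputs. On prevalence: "We expect that 8% of this population will have NAFLD and 2% will have liver fibrosis". On numbers available, after assuming blood from half the sample: "This will add up to 1,433 blood tests and 424 MRIs". The calculation is described as "assuming a design effect of 20%, an alpha error of 5%, a power of 80% and bilateral contrasts".

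The statistical analyses section names the pairs for which kappa will be used: "CAP vs FLI, LSM vs PNFI, LSM vs PNFS) will be assessed by kappa indices". It also says that missing data will not be imputed. The section on measuring tools builds FLI partly on triglycerides and GGT, and groups PNFI and PNFS under serum biomarkers.

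**The concern.** Two features of the design work against a single 4% figure. First, every pair listed for kappa includes a score that needs blood. With no imputation, a child without a blood sample drops out, so n is at most about 1,433 and not 2,866. Second, the standard error of kappa rises steeply as the condition becomes rarer, and the protocol expects only 8% and 2% positive.

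Agreement between VCTE and the serum scores is among the specific outcome measures. A reader who takes the stated 4% at face value expects a kappa of 0.80 to be reported with an interval of about 0.76 to 0.84. For the fibrosis scores, about 29 LSM-positive children are expected to have blood (0.02 × 1,433 = 28.7), and the interval will be about three times as wide.

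**Working it through.** **Inputs, all from the protocol article.** Kappa k = 0.80. n = 2,866 enrolled, 1,433 with blood, 424 with MRI. Prevalence p = 0.08 (steatosis) and 0.02 (fibrosis). Design effect (DEFF) 1.2. Two-sided 5%, so z = 1.96.

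**What precision means here.** The section's prevalence precisions were checked first. With four strata, n = 2,866/4 = 716.5:
- 8%: 1.96 × √(0.08 × 0.92 / 716.5) = 1.99 points (stated: 2)
- 2%: 1.96 × √(0.02 × 0.98 / 716.5) = 1.03 points (stated: 1)

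So precision is the 95% half-width.

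**Formula.** For two binary ratings with equal margins p, the large-sample variance of kappa is

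Var = (1−k) × [(1−k)(1−2k) + k(2−k) / (2p(1−p))] / n

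and the half-width is 1.96 × √(Var × DEFF). At k = 0.80 the numerator reduces to 0.2 × [−0.12 + 0.48/(p(1−p))]:
- p = 0.08: 0.2 × (6.522 − 0.12) = 1.280
- p = 0.02: 0.2 × (24.490 − 0.12) = 4.874

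The value at p = 0.08 is identical under the general Fleiss-Cohen-Everitt variance.

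**The stated 4%, tried with the full sample.**
- 8%, n = 2,866: 1.96 × √(1.280/2,866) = 4.14 points; with DEFF 1.2, 4.54. Adding a finite-population correction for 11,503 pupils gives about 3.9.
- 2%, n = 2,866: 1.96 × √(4.874/2,866) = 8.08 points; with DEFF 1.2, 8.85.

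So 4% is roughly the steatosis figure if every child had both measures. It is not the fibrosis figure on any sample the study will have.

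**The planned comparisons, n = 1,433.**

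| Comparison | Prevalence | DEFF 1 | DEFF 1.2 |
|---|---|---|---|
| CAP vs FLI | 8% | 1.96 × √(1.280/1,433) = 5.86 | 6.42 |
| LSM vs PNFI, LSM vs PNFS | 2% | 1.96 × √(4.874/1,433) = 11.43 | 12.52 |

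With DEFF 1.2, the interval around a fibrosis kappa of 0.80 is 0.80 ± 0.125, or roughly 0.67 to 0.93.

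**Robustness.**
- DEFF 1.2 with finite-population correction: about 6.0 and 11.7 points.
- Multinomial simulation, 200,000 draws: 5.9 and 11.8 without DEFF, 6.5 and 13.0 with it.
- Moderately unequal margins (8% against 6%, 10% or 11%; 2% against 1.5% or 2.5%), DEFF 1 to 1.2: 5.4 to 6.8 and 10.8 to 13.4 points.

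**The MRI figure.** The 424 is reproduced by 8% of 2,866 = 229 CAP-positive children at 70% uptake, plus 10% of the other 2,637 = 264: 0.7 × 229 + 264 = 424. About 160/424 = 38% of that subset is then CAP-positive. At p = 0.38 and n = 424 the half-width is 5.9 points (DEFF 1) or 6.5 (DEFF 1.2), inside the stated 8%.

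**The case against.** The strongest reply is that the proposed sample means all 2,866 children, and that the 4% is then about right at 8% prevalence. The arithmetic stands: 4.1 to 4.5 points. It does not rescue the figure, because none of the three listed kappas can use 2,866 children when half are expected to lack blood, and because fibrosis misses 4% by a factor of about two even at 2,866.

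The same result rules out a stronger reading. At n = 1,433 a half-width of 4 points needs a prevalence of about 19% (DEFF 1) to 24% (DEFF 1.2), so a reader might infer that the authors assumed some 20 to 25% positive, against their own 8% and 2%. The document states no such prevalence, and the full sample at 8% comes close to 4% without it. Which route was taken cannot be told from the text.

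A second reply is that precision might mean one standard error. That would give about 3 points for steatosis at n = 1,433, but it does not fit the prevalence precisions in the same section, and fibrosis would still be 5.8 to 6.4.

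A third reply has force. The figures of 6 and 12 points assume similar positivity for both methods. The protocol gives no expected positivity for FLI, PNFI or PNFS, and it will choose the PNFI and PNFS cut-offs afresh from ROC curves. If the margins differ widely, a kappa of 0.80 cannot be reached at all: margins of 2% and 5% cap kappa at 0.56, and 8% and 4% cap it at 0.65. The replacement figures must therefore be printed with their assumptions.

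**Conclusion.** The point holds for the three blood-based kappas. The half-width is about 1.5 times the stated 4 points for CAP vs FLI and about three times for LSM vs PNFI and PNFS. This rests on kappa 0.80 (the protocol's own value), the protocol's prevalences, 1,433 children with blood, and roughly equal margins.

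Two further inferences are not supported. One is that the 8% for the MRI subset is also wrong, since at the population prevalence of 8% the half-width for 424 children would be 10.8 to 11.8 points. That subset takes all VCTE positives and only a tenth of negatives, so the population prevalence does not apply to it. CAP vs MRI is also not among the pairs listed for kappa. The other is that the study cannot report on fibrosis-score agreement. The protocol sets no agreement threshold or hypothesis, and a wide interval is still informative.

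The affected comparisons are specific outcomes. The prevalence precisions to which the 2,866 is tied reproduce, so the sample size itself is not in question. The correction should be made, but it does not touch the main aims.

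**What to change.** In the sample size section, replace the single 4% with a statement per comparison at n = 1,433: about ±6 points for CAP vs FLI (8% prevalence) and about ±12 points for LSM vs PNFI and LSM vs PNFS (2% prevalence). State beside these the assumed kappa of 0.80, equal margins and the design effect of 1.2, and say that the fibrosis-score agreement will have a wide interval. Leave the MRI figure as it is.

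The cost is a few lines of text. No subjects, visits or analyses are added. The only consequence is that the stated precision becomes less favourable.

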Diagnosis of NAFLD should be considered in paediatric population with excess weight, especially in those >10 years of age, with arterial hypertension (AHT), DM, IR or metabolic syndrome (MetS). In clinical practice, screening begins with anamnesis, physical examination, blood test and abdominal ultrasound, which help to establish a differential diagnosis with other entities. However, liver biopsy remains the gold standard for assessing disease progression, although its use is limited by its invasiveness and potential complications [8]. Some authors consider screening with transaminases, but these may still be normal in patients with NAFLD [5]. In terms of imaging, abdominal ultrasound, which is an affordable and safe technique, is only able to detect fatty infiltration above 30% [9]. Magnetic resonance imaging (MRI) is more accurate in diagnosing NAFLD, showing high sensitivity and specificity [10]. Nevertheless, its high cost and limited availability make it an invalid method for population screening.

Therefore, non-invasive serological and elastographic diagnostic methods are being developed. The most widely used is Vibration-Controlled Transient Elastography (VCTE), which non-invasively determines the presence of fibrosis by measuring liver stiffness (LSM) with the FibroScanⓇ (FS) device [11]. Multiple studies have demonstrated its usefulness in adults [11, 12], so it may also be appropriate for children and adolescents [5, 11]. Normal LSM values may vary according to age, ranging from 3.4–5.1 kPa [13, 14, 16]. Above this threshold, values correlate with different stages of fibrosis on the METAVIR scale: 5–7 kPa is indicative of F1; 7–9 kPa, F1-F2; and >9 kPa, F3-F4 [15, 16]. FibroScan features the Controlled Attenuation Parameter (CAP), which allows quantification of hepatic fat >11%. CAP values correlate with the degree of steatosis and a cut-off point of ≥225 dB/m is used for its detection [17, 18]. Furthermore, serological markers are used for diagnostic approaches to NAFLD and fibrosis. In adults, the Fatty Liver Index (FLI) [19] (NAFLD) as well as the NAFLD Fibrosis Score and FIB-4 (fibrosis) are commonly used [20] but these do not provide accurate results in the paediatric population [8, 21]. Thus, specific markers have been developed for these patients, such as the Pediatric NAFLD Fibrosis Index (PNFI) [22] and the Pediatric NAFLD Fibrosis Score (PNFS) [23], with an AUROC of 0.85 and 0.74 respectively [22, 23].

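### The kappa of 0.80 with 4% precision does not hold for liver stiffness against PNFI and PNFS: at 2% fibrosis on 1,433 blood samples the half-width is about 0.125, and 0.80 itself is unrealistic

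*Protocol article*

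**What the plan says.** The Sample size calculation gives a single planning statement for agreement: "With the proposed sample we can find a concordance of 80% with a precision of 4% using kappa indices". A parenthesis adds "8% and 4% precision for kappa and ICC, respectively, using only 424 MRIs". The sentence names no pair of methods and no positive rate. The same section supplies the other inputs: "We expect that 8% of this population will have NAFLD and 2% will have liver fibrosis"; "This will add up to 1,433 blood tests and 424 MRIs"; and the calculation was made "assuming a design effect of 20%, an alpha error of 5%, a power of 80% and bilateral contrasts".

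Under Statistical analyses, the dichotomised diagnoses from three pairs (CAP vs FLI, LSM vs PNFI, LSM vs PNFS) "will be assessed by kappa indices (when using the dichotomised version of these variables" are used. CAP against MRI is handled by ANOVA, ROC curves and chi-square tests instead. The same section plans ROC curves for PNFI and PNFS with LSM ≥6.5 kPa as the standard. The Introduction credits PNFI and PNFS "with an AUROC of 0.85 and 0.74 respectively", without naming the reference standard or population.

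**The concern.** Kappa is the planned measure for only three pairs, and two of them are the fibrosis scores. The 0.80 with 4% precision is therefore the only planning basis the protocol gives for those two. It should then be consistent with 2% fibrosis, with the half of the sample that has blood, and with the accuracy the Introduction reports for the scores.

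Two things are at stake. A reader would expect an agreement estimate about three times as precise as the data can give. And 0.80 would become the natural yardstick for two scores that, on the protocol's own figures, would be expected to fall far below it in a population with 2% positives.

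**Working it through.** **Inputs.** Kappa 0.80 and precision 0.04 (0.08 on 424 MRIs); fibrosis 2%, NAFLD 8%; total sample 2,866; blood samples 1,433; design effect 1.2; population 11,503 in four roughly equal strata (all from Sample size calculation). AUROC 0.85 (PNFI) and 0.74 (PNFS), from the Introduction. The scores are serum markers, so their pairs have at most 1,433 children, of whom 0.02 × 1,433 ≈ 29 are expected to have LSM ≥6.5 kPa.

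**The plan's main figure.** Fibrosis 2% ± 1% per stratum: n₀ = 1.96² × 0.02 × 0.98 / 0.01² = 753. With a finite population of 11,503/4 = 2,876 this becomes 597; × 1.2 = 716; × 4 strata = 2,865, against 2,866 stated. The sample size therefore comes from prevalence, not from kappa.

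**Precision of kappa.** Large-sample variance of a 2×2 kappa (Fleiss–Cohen–Everitt) with equal margins p:

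var = (1−κ)/n × [(1−κ)(1−2κ) + κ(2−κ)/(2p(1−p))].

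For κ = 0.80 and p = 0.02 the bracket is −0.12 + 0.96/0.0392 = 24.37. With n = 1,433/1.2 = 1,194, var = 0.2 × 24.37/1,194 = 0.00408, SE = 0.0639 and the half-width is 1.96 × 0.0639 = 0.125. Without the design effect it is 0.114. Other cases, with design effect 1.2:

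| Positives | n = 2,866 | n = 1,433 | n = 424 |
|---|---|---|---|
| 2% | 0.089 | 0.125 | 0.230 |
| 8% | 0.045 | 0.064 | 0.118 |
| 20% | 0.030 | 0.043 | 0.079 |

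The stated pair of 0.04 and 0.08 appears only near 20% positives on 1,433 and 424. The 0.04 alone is also approached at 8% positives on all 2,866 (0.045; 0.041 without the design effect), but neither that rate nor that number applies to the fibrosis pairs.

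A lower kappa does not rescue the precision. At κ = 0.23 the bracket is 0.416 + 0.407/0.0392 = 10.80, var = 0.77 × 10.80/1,194 = 0.00697, and the half-width is 0.164.

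**Attainable kappa at 2%.** With π the prevalence and q = π·Se + (1−π)(1−Sp) the score-positive rate,

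κ = 2π(1−π)(Se + Sp − 1) / (π + q − 2πq).

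Maximised over all cut-offs of an equal-SD binormal ROC:

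- PNFI (0.85): Se 0.265, Sp 0.982, q = 0.0232, κ ≈ 0.0392 × 0.247/0.0422 = 0.23.
- PNFS (0.74): Se 0.165, Sp 0.970, q = 0.0325, κ ≈ 0.0392 × 0.135/0.0512 = 0.10.

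Sensitivity to assumptions (maximum kappa):

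| Assumption | PNFI | PNFS |
|---|---|---|
| Prevalence 1% to 5%, equal SD | 0.17–0.33 | 0.07–0.17 |
| 2%, SD in cases ×1.5 | 0.40 | 0.24 |
| 2%, SD in cases ×2 | 0.53 | 0.36 |
| 2%, SD in cases ×5 | 0.78 | 0.65 |
| 2%, any concave ROC (bound) | 0.82 | 0.64 |
| 50%, equal SD | 0.54 | 0.35 |

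The bound uses Se − (1−Sp) ≤ 2·AUROC − 1, taken at Sp = 1. For PNFI, Se = 0.70 and q = 0.014 give 0.02744/0.03344 = 0.82. For PNFS, Se = 0.48 and q = 0.0096 give 0.01882/0.02922 = 0.64.

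**What 0.80 would need at 2%.** Specificity of at least 99.9% at sensitivity 70%, 99.3% at 90%, or 99.0% at 100%. On an equal-SD binormal curve that is an AUROC of about 0.993.

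**The case against.** The sentence is a generic precision statement. It forecasts nothing for the fibrosis scores and sets no pass mark, and the protocol has no scale that labels a kappa good or poor. That stands: a reader might infer that 0.80 is a target for PNFI and PNFS, and the text does not say so. It remains the only planning figure for the pairs assigned to kappa, and its precision is wrong for two of the three.

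A reader might also infer that 0.80 is impossible, or that kappa would be low however good the scores were. Neither is supported. For PNFI a concave ROC allows up to 0.82, though only with 70% sensitivity and no false positives. And kappa does respond to accuracy: sensitivity 90% with specificity 99.5% gives 0.84 at 2% prevalence. At 50% prevalence the cited AUROCs would still give at most 0.54 and 0.35, so prevalence is not the only cause.

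The AUROCs are literature values with no stated reference standard or population, so applying them to LSM in schoolchildren is an assumption. The precision result does not depend on it.

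Finally, discrimination is already to be analysed by ROC curves, and the plan does not say that kappa will be computed at the ROC-chosen cut-off; it also lists literature cut-offs (PNFI ≥9, PNFS ≥13). Kappa values worked out at a Youden cut-off would therefore rest on a rule the plan does not state, and none is relied on here.

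**Conclusion.** The kappa statement is wrong as written for LSM vs PNFI and LSM vs PNFS. At 2% positives on 1,433 blood samples the half-width at kappa 0.80 is about 0.125, roughly three times the stated 0.04. This uses only the protocol's figures, equal margins and a large-sample formula; with about 29 positives that formula is itself approximate.

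The value 0.80 is also unrealistic for these pairs. If the cited AUROCs carry over, it is excluded for PNFS under any concave ROC and implausible for PNFI. The exact ceiling depends on the ROC shape, so 0.23 and 0.10 are results under the equal-SD model and not properties of the scores. A low observed kappa would reflect both the low prevalence and the scores' modest accuracy.

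The consequence is limited. These are specific outcomes, the sample size follows from the prevalence aims, and no main outcome is affected.

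**What to change.** In Sample size calculation:

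- State which comparison and which positive rate the 80% with 4% precision refers to.
- Withdraw it for LSM vs PNFI and LSM vs PNFS, and give the precision at 2% positives on 1,433 samples instead: about ±0.12 or wider.
- Do not print an attainable kappa as fact, because it depends on the ROC shape.

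In Statistical analyses:

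- Base conclusions about PNFI and PNFS on the ROC analysis already planned: AUC, sensitivity and specificity with 95% confidence intervals against LSM ≥6.5 kPa, at the literature cut-offs (PNFI ≥9, PNFS ≥13) and at the ROC-chosen cut-off.
- Report kappa for these pairs as description, with positive and negative agreement beside it.

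The cost is wording only, with the same data and the same sample size. The downside is that the printed precision becomes less favourable.
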